#### Secondary endpoints:

- 1) QoR-15 scores at 48 and 72 h postoperatively,
- 2) cumulative opioid consumption (MME) at 24, 48, and 72 h postoperatively,
- 3) total intraoperative opioid dosage,
- 4) NRS scores during rest or movement in the post-anesthesia care unit (PACU) or at 24, 48, and 72 h postoperatively,
- 5) time to first flatus,
- 6) time to first ambulation,
- 7) supplementary analgesic dosage at 24, 48, and 72 h postoperatively,
- 8) adverse events (dizziness/headache, nausea/vomiting, pruritus, hypotension) at 24, 48, and 72 h postoperatively and
- 9) length of hospital stay.

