## 6 Sample Size

The primary outcome measure was the QoR-15 score at 24 h postoperatively. Based on previous literature and the results of pilot experiments, the minimum clinically important difference (MICD) of the QoR-15 score was determined to be 6.0. The standard deviation (SD) of the QoR-15 score after major surgery ranged from 10 to 16. Taking a conservative estimate, we selected an SD of 16. Assuming  $\alpha = 0.05$  and  $\beta = 0.2$  (with a power of 80% to detect this difference), calculations were performed using PASS 21 software. The result indicated that 113 patients were required in each group. Considering a 10% dropout rate, our target was a final sample size of 252.

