### 7.6 Confidence Intervals and p-values

All estimates of differences between groups would be presented with two-sided 95% confidence intervals unless otherwise stated. Statistical significance will be considered if  $p < 0.05$  (two-sided).

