## 198 9 Efficacy Analyses

199 This analysis adhered to the intention-to-treat (ITT) and per-protocol principle.  
200 Continuous quantitative data were described as mean  $\pm$  standard deviation if  
201 normally distributed, with between-group comparisons performed using  
202 independent t-tests. Non-normally distributed data were summarized as median  
203 (P25, P75) and analyzed using the Wilcoxon rank-sum test. Categorical variables  
204 were expressed as frequencies (percentages), with group comparisons conducted  
205 via Chi-square tests or Fisher's exact test, as appropriate. Ordinal data were  
206 similarly described as frequencies (%) and compared using the rank-sum test.

207 For the primary outcome, intergroup differences were assessed using a generalized  
208 estimating equation (GEE) model implemented via the R package geepack, with an  
209 exchangeable correlation structure. The model incorporated time, group, their  
210 interaction (time  $\times$  group), and adjustments for age, sex, weight, ASA classification,  
211 complications, anesthesia duration, and baseline values. Estimated marginal means  
212 at each time point were visualized using line plots, either as absolute values or  
213 relative changes from baseline.

214 Binary outcomes were reported as counts (%) and analyzed using generalized linear  
215 models to estimate rate differences (RDs) with 95% CI, adjusting for age, sex,  
216 weight, ASA status, complications, and anesthesia duration. For ordinal outcomes,  
217 between-group comparisons employed the rank-sum test, with median differences  
218 and 95% CI calculated. Single-measurement continuous outcomes were analyzed via

219 linear regression, adjusting for the same covariates.

220 Longitudinal outcomes lacking baseline measurements were evaluated using GEE  
221 models (exchangeable correlation) with time, group, their interaction, and  
222 covariates (age, sex, weight, ASA, complications, anesthesia duration). Estimated  
223 trends were plotted by group. All analyses and visualizations were performed in R  
224 (v4.4.1).

225 Results of efficacy analyses will be presented as tables or in text in the final  
226 publication(s), including p-values.

227 9.1 Primary Efficacy Analysis

228 Analysis of primary endpoint (xx) will be performed in accordance with section 9.

229 9.2 Secondary Efficacy Analyses

230 Analyses of secondary endpoints will be performed in accordance with section 9.

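### For cumulative MME, one covariate coefficient shared by 24, 48 and 72 h can cost part of the 24 h precision gain; time-specific coefficients would avoid this

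*SAP*

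**What the plan says.** SAP section 4.2 lists as a secondary endpoint "cumulative opioid consumption (MME) at 24, 48, and 72 h postoperatively". It has three measurements per patient and no baseline value, so it falls under the section 9 rule for longitudinal outcomes without baseline: GEE "models (exchangeable correlation) with time, group, their interaction, and" then "covariates (age, sex, weight, ASA, complications, anesthesia duration). Estimated". The only interaction is between time and group.

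The primary QoR-15 model has the same structure, with baseline added to the adjustment list: "complications, anesthesia duration, and baseline values. Estimated marginal means".

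Section 9 also provides that continuous outcomes measured once are analysed by linear regression with the same covariates. For the GEE models it names the R package, the working correlation and the model terms, but no link function and no transformation.

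**The concern.** The group effect may differ at each time point, but each covariate effect is held constant over time. For a running total that constraint is unlikely to fit on the absolute scale. A covariate that shifts opioid use by some amount on each day shifts the 72 h total by more than the 24 h total. A single coefficient must compromise between them, and the compromise is too large for 24 h. Chance imbalance in the covariate between arms is then over-corrected in the 24 h contrast.

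What is at stake is precision: the confidence interval for the 24 h MME difference may be wider than the same data and covariates allow.

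**Working it through.** **The plan's own figure.** The SAP states no number for MME, so the only figure to reproduce is the sample size in section 6: "MICD) of the QoR-15 score was determined to be 6.0"; "Taking a conservative estimate, we selected an SD of 16"; "with a power of 80% to detect this difference"; two-sided 0.05. The normal approximation gives 112 per group. The noncentral t gives 113 (power 0.801). Then 113/0.9 rounds up to 126 per group, or 252 in total. The figure reproduces and this point does not affect it.

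**Inputs.** From the SAP: the model terms and exchangeable correlation (section 9), cumulative MME at three times (section 4.2), and 113 per group (section 6). Assumed: identity link, complete data, the change in daily covariate effects, and the share R² of 24 h variance that the covariates explain.

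**Step 1: the shared coefficient.** Let b1, b2, b3 be a covariate's effects on the 24, 48 and 72 h totals. With patient-level covariates, complete data and exchangeable correlation, the fitted coefficient is m = (b1 + b2 + b3)/3. A fitted GEE agreed with this to about 1e-14.

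**Step 2: share of the 24 h gain lost.** Correct adjustment removes b1²·var(X) from the 24 h variance. The shared coefficient leaves (b1 − m)²·var(X). The share lost is therefore L = (m/b1 − 1)².

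Suppose the daily effect is multiplied by r each day, so the cumulative effects are 1, 1 + r, 1 + r + r²:

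| r | Cumulative effects | m/b1 | L at 24 h |
|---|---|---|---|
| 1 (constant) | 1, 2, 3 | 2.00 | 100% |
| 0.8 | 1, 1.80, 2.44 | 1.75 | 56% |
| 0.7 | 1, 1.70, 2.19 | 1.63 | 40% |
| 0.5 | 1, 1.50, 1.75 | 1.42 | 17% |
| 0 (day 1 only) | 1, 1, 1 | 1.00 | 0% |

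L exceeds one half only for r above about 0.77. If daily effects grow (r = 1.2), L is 164%, which is worse than no adjustment.

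**Step 3: effect on the 24 h standard error.** Relative to time-specific coefficients, the SE ratio is √(1 + L·R²/(1 − R²)). For example, r = 1 and R² = 0.20 give √(1 + 0.20/0.80) = 1.118.

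| Increase in 24 h SE | R² = 2% | 5% | 10% | 20% |
|---|---|---|---|---|
| r = 1 | 1.0% | 2.6% | 5.4% | 11.8% |
| r = 0.7 | 0.4% | 1.0% | 2.2% | 4.8% |
| r = 0.5 | 0.2% | 0.5% | 1.0% | 2.2% |
| r = 0 | 0% | 0% | 0% | 0% |

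**Step 4: simulation check.** With 226 patients, 600 runs, r = 1 and R² = 0.2, the SD of the 24 h contrast was 0.301 unadjusted, 0.308 with the shared coefficient and 0.268 with time-specific coefficients. Across the settings run, the shared-coefficient estimate showed no material bias, and robust-SE rejection under the null was 3% to 7%, consistent with 5% for 600 runs.

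**Step 5: other time points and outcome.** At r = 1 the loss is (2/2 − 1)² = 0 at 48 h and (2/3 − 1)² = 11% of the gain at 72 h. For QoR-15 at 24 h, assuming baseline correlations that rise from 0.15–0.3 at 24 h to 0.5–0.6 at 72 h, the loss is about 0.1% to 3% of the SE.

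**The case against.** The best defence is that covariate main effects in a repeated-measures GEE are a valid choice. Randomisation keeps the contrast unbiased, and the robust standard error reflects whatever precision the model achieves. That stands: this is a question of efficiency only.

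Three further objections limit the point:

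- **Size.** All magnitudes are assumed. A reader might infer that the 24 h contrast loses most or all of its adjustment gain. The documents do not support that, because it requires daily covariate effects that fall by less than about 23% per day, and the SAP says nothing about their course. With daily use of 30, 20 and 15 mg (an assumed pattern) and covariate effects in proportion, m/b1 = (30 + 50 + 65)/3/30 = 1.61 and L = 0.61² = 37%, so most of the gain is kept.
- **Scale.** The SAP names no link. With a log link and constant proportional covariate effects, the coefficients would be equal at all times and the problem would vanish. Identity is the natural reading, but it is an assumption. Section 9 also sends non-normal continuous data to the rank-sum test and does not say which rule governs a skewed MME.
- **Importance.** Cumulative MME is one of nine secondary endpoints that the SAP does not rank, so nothing marks its 24 h value as a leading result.

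None of these removes the mechanism. Under an identity link, some 24 h precision is lost whenever a covariate that acts on day 1 keeps acting in the same direction.

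**Conclusion.** The point holds as a conditional efficiency loss in a secondary endpoint. Under an identity link and complete data, the planned model over-corrects the 24 h MME contrast if covariate effects persist after day 1. The share of the adjustment gain lost runs from 0% (day 1 only) to 100% (constant daily effects). For R² up to 20%, the 24 h SE is larger by roughly 0 to 10%, and the closed form reaches 12% at the most unfavourable end of that range.

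A reader might also infer that the MME analysis is invalid or the primary result compromised. Neither follows: the estimate is unbiased, robust inference is valid, 48 h is essentially unaffected, 72 h changes little, and the QoR-15 loss is small. With missing visits the averaging is no longer exact. Section 6 allows for 10% dropout and section 7.4 rules out imputation, so the figures are approximate for the trial as it will be observed.

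**What to change.** In section 9, for cumulative MME, do one of the following:

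- estimate the group difference at each of 24, 48 and 72 h by a separate adjusted linear regression, as the section already does for single-measurement outcomes; or
- keep the GEE and add covariate by time terms for every covariate retained in the model. Interacting only age, sex, weight and ASA would leave the problem in place for complications and anesthesia duration, and would not match the separate regressions.

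The two options agree for complete data. State the link function in either case. A baseline QoR-15 by time term in the primary model is optional, since the gain there is small.

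The cost is a sentence of SAP wording, a small code change and two extra parameters per covariate term. Counting ASA I to III as two contrasts and complications as a single indicator (an assumption), there are seven terms, so 14 extra parameters on 226 to 252 patients. No new data are needed.

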| Medical history taking                 | ×                  |                |                 |              |              |              |                         |                                       |
| Allocation                             |                    | ×              |                 |              |              |              |                         |                                       |
| INTERVENTIONS                          |                    |                |                 |              |              |              |                         |                                       |
| Intrathecal morphine or salute         |                    | ×              |                 |              |              |              |                         |                                       |
| Transversus abdominis plane block      |                    | ×              |                 |              |              |              |                         |                                       |
| ASSESSMENTS                            |                    |                |                 |              |              |              |                         |                                       |
| QoR-15 scores                          | ×                  |                |                 | ×            |              | ×            |                         |                                       |
| NRS                                    |                    |                | ×               | ×            |              | ×            |                         |                                       |
| Total opioid consumption               |                    |                |                 | ×            |              | ×            |                         |                                       |
| Time of the first flatus               |                    |                |                 |              | ×            |              |                         |                                       |
| Time of the first ambulation           |                    |                |                 |              | ×            |              |                         |                                       |

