| Amount of analgesic drugs supplemented |                    |                | ×               | ×            |              | ×            |                         |                                       |
| Adverse events                         |                    |                |                 | ×            |              | ×            |                         |                                       |
| Length of hospital stay                |                    |                |                 |              |              |              | ×                       | ×                                     |

Fig. 2 Time schedule of enrolment, interventions, assessments and visits for participants

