## 5.3 Randomization and Blinding

Potential trial participants were identified by a research team member through electronic medical record screening. Eligible patients were approached, and written informed consent was obtained either before surgery. Patients were randomly allocated in a 1:1 ratio to receive either the intervention group or the control group using Sun Yat–sen University Cancer Center' s (SYSUCC) interactive web–based response system (IWRS). Allocation concealment was ensured by restricting researcher access to the randomization system until study completion. An independent research assistant conducted randomization using sequentially numbered, opaque envelopes containing group assignments. Based on group assignments, the pharmacist prepared identical 5 mL intrathecal solutions (normal saline or morphine) in 10 mL syringes for administration. To ensure blinding, the administering anesthesiologist was excluded from subsequent procedures and data collection. An independent researcher, blinded to group allocation and uninvolved in interventions or analysis, collected all outcome data.

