## 8.1 Protocol Deviations

Major deviations are defined as follows:

- Wrong treatment in contrast to randomization.
- Violation of inclusion and exclusion criteria.
- Missing informed consent.

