231 9.3 Exploratory Efficacy Analyses

232 Further analysis of exploratory analyses will be performed in accordance with  
233 section 9.

234

235 10 Safety Analyses

236 All adverse events which are directly connected to study procedures will be  
237 documented and reported by appropriate statistical methods in accordance with  
238 section 9.

239

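### Section 10 reports adverse events only through an undefined causal filter, does not say how this relates to the unfiltered secondary endpoint 8, and gives no safety tabulation by treatment received

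*SAP*

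**What the plan says.** Section 10 (Safety Analyses) is a single sentence. It begins "All adverse events which are directly connected to study procedures will be" and goes on to say that these events are documented and reported with suitable methods under section 9. It does not define study procedures or a direct connection, and it does not say who judges the connection or when.

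Section 4.2 lists as secondary endpoint 8: "adverse events (dizziness/headache, nausea/vomiting, pruritus, hypotension) at 24, 48, and 72 h postoperatively". No causal condition is attached. The assessment schedule in section 5.1 has a row "Adverse events", also without one.

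Section 9.2 sends the secondary endpoints to section 9. Section 9 analyses binary outcomes as counts and adjusted rate differences with 95% CI, sets no relatedness condition, and names the intention-to-treat and per-protocol principles. Section 8.1 lists "Wrong treatment in contrast to randomization" first among the major deviations.

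On design, section 5.3 states "Patients were randomly allocated in a 1:1 ratio" and "An independent researcher, blinded to group allocation and uninvolved in interventions or analysis, collected all outcome data".

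**The concern.** Every patient in this trial has laparoscopic colorectal surgery under general anesthesia. When one of them has an adverse event, it usually cannot be settled at the bedside whether the intrathecal drug, the block, the anesthetic or the operation caused it. Randomization with blinding removes the need to settle it: causes other than the allocated drug are balanced in expectation between arms, so a comparison of all events by arm estimates the effect of the drug. A filter applied event by event before that comparison replaces it with individual opinion. Because section 10 defines neither the criterion nor the assessor, that opinion could not be reproduced.

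The plan also has two scopes for adverse events and no sentence linking them. Two analysts could read endpoint 8 differently, one counting all nausea/vomiting and the other counting only what passed the section 10 filter.

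At stake is the completeness of the harms report, above all for events outside the four named groups.

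**Working it through.** No figure in the SAP bears on this point. The sample size in section 6 rests on the QoR-15 difference and SD, not on adverse events. For completeness, it reproduces: a difference of 6.0 and SD of 16 at two-sided 0.05 and 80% power give 112.6 per group by the t-test, rounded up to 113; 113/(1 − 0.10) = 125.6, rounded up to 126 per group, or 252 in total. The check is therefore a comparison of the text.

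**Step 1. The scopes side by side.**

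| Place in the SAP | Events covered | Causal condition |
|---|---|---|
| 4.2, secondary endpoint 8 | Four named groups at 24, 48 and 72 h | None |
| 5.1, assessment schedule | Adverse events, unspecified | None |
| 9 and 9.2 | Binary outcomes and secondary endpoints | None |
| 10 | All types | Direct connection to study procedures |

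**Step 2. An event inside the four groups.** It reaches the report through endpoint 8, section 9.2 and section 9, none of which filters by cause. If endpoint 8 is analysed as listed, the event is counted. The SAP does not say that endpoint 8 stands apart from section 10, so this is the natural reading and not a stated rule.

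**Step 3. An event outside the four groups.** Endpoint 8 does not name it. The schedule row may cover its recording but prescribes no analysis. The one provision for reporting it is section 10, so under this SAP it is reported only if judged connected. This holds for a serious event as for a minor one.

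**Step 4. What blinding does and does not do.** A blinded assessor is unlikely to attribute events differently by arm because of knowledge of allocation. That limits bias from the filter. It does not bring back the events that the filter removes, and it does not supply the missing criterion.

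**Step 5. Analysis set.** Section 10 defers to section 9, which names intention-to-treat and per-protocol. Take a patient randomized to saline who receives morphine, the kind of deviation that section 8.1 describes. Under intention-to-treat, any event counts in the saline arm. A per-protocol set may drop the patient. Neither shows the event against the drug received.

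**The case against.** The strongest reply is that the two scopes can coexist. Endpoint 8 is listed without a filter, has its own route to analysis, and is collected by a blinded researcher; section 10 then adds to it. This stands for the four groups, and for that reason the passages are better described as unreconciled than as contradictory.

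A reader might infer that events put down to surgery are never recorded. The SAP does not say so. Section 10 says what will be documented and is silent on the rest; endpoint 8 and the schedule call for recording without regard to cause; and the protocol, not shown, may collect events more widely.

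A reader might also infer a definite loss of power. The documents do not support one. Suppose, purely as an assumption, true rates of 30% v 45% with 126 per arm. If half of all events are judged connected in each arm, these become 15% v 22.5%: the difference falls from 15 to 7.5 points and power from 69% to 33%. If instead 20% of background events and 90% of drug-caused events are judged connected, the rates become 0.20 × 30% = 6% and 6% + 0.90 × 15% = 19.5%: the difference is 13.5 points and power is 90%. The direction of the change in power thus depends on an assumption that the SAP does not inform. Such a calculation for a named event such as nausea/vomiting would also miss the point, since endpoint 8 covers it.

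Finally, collection windows and the handling of serious events commonly belong to the protocol, so their absence here is no fault. What the SAP does state is a restriction on reporting, and that can be reviewed. It is also fair to say that section 8.1 defines wrong treatment without predicting it; the treatment-received point is secondary and may concern no patient at all.

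**Conclusion.** The point holds in a limited form. Three things follow from the text: events outside the four groups in endpoint 8 are reported under this SAP only through a causal judgement that is undefined; the relation between section 10 and endpoint 8 is unstated; and safety is analysed with no tabulation by treatment received.

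No numerical size can be given, because the SAP contains no event rates and no share judged connected. The conclusion assumes that endpoint 8 is analysed as listed, and that the protocol does not already override the reporting rule in section 10. If it does, the SAP should say so. It is a change that should be made to the harms report; it does not affect the primary analysis.

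**What to change.** Reword section 10 along these lines: all recorded adverse events, serious ones included, are reported by arm regardless of judged cause; relation to study procedures, judged blind to allocation, is tabulated separately. Define there what counts as a study procedure and who makes the judgement.

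Add one sentence to section 4.2 or section 10 stating that endpoint 8 counts its four event groups regardless of cause.

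Add that, if any wrong-treatment deviation under section 8.1 occurs, safety is also tabulated by treatment received.

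The collection period stays with the protocol. The cost is a few sentences in the SAP and a longer adverse-event table.
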